## Abstract

**Background:**

Foot complications occur in conjunction with poorly controlled diabetes. Plantar forefoot ulceration contributes to partial amputation in unstable diabetics, and the risk increases with concomitant neuropathy. Reducing peak plantar forefoot pressure reduces ulcer occurrence and recurrence. Footwear and insoles are used to offload the neuropathic foot, but the success of offloading is dependent on patient adherence. This study aims to determine which design and modification features of footwear and insoles improve forefoot plantar pressure offloading and adherence in people with diabetes and neuropathy.

**Methods:**

This study, involving a series of N-of-1 trials, included 21 participants who had a history of neuropathic plantar forefoot ulcers. Participants were recruited from two public hospitals and one private podiatry clinic in Sydney, New South Wales, Australia. This trial is non-randomised and unblinded. Participants will be recruited from three sites, including two high-risk foot services and a private podiatry clinic in Sydney, Australia. Mobilemat™ and F-Scan® plantar pressure mapping systems by TekScan® (Boston, USA) will be used to measure barefoot and in-shoe plantar pressures. Participants’ self-reports will be used to quantify the wearing period over a certain period of between 2 and 4 weeks during the trial. Participant preference toward footwear, insole design and quality-of-life-related information will be collected and analysed. The descriptive and inferential statistical analyses will be performed using IBM SPSS Statistics (version 27). And the software NVivo (version 12) will be utilised for the qualitative data analysis.

**Discussion:**

This is the first trial assessing footwear and insole interventions in people with diabetes by using a series of N-of-1 trials. Reporting self-declared wearing periods and participants’ preferences on footwear style and aesthetics are the important approaches for this trial. Patient-centric device designs are the key to therapeutic outcomes, and this study is designed with that strategy in mind.

**Trial registration:**

Australian New Zealand Clinical Trials Registry (ANZCTR) ACTRN12620000699965p. Registered on June 23, 2020

## Background

Foot ulcers are a common consequence of diabetes due to the development of peripheral neuropathy, peripheral vascular disease, limited joint mobility and foot deformity [2–7]. Nearly 34% of people with diabetes will develop a foot ulcer in their lifetime [8]. This can lead to infection and amputation; diabetes is the main reason for non-traumatic amputation [9, 10]. Previous foot ulceration or amputation is a risk for future amputation [2, 4, 6, 11]. Additional risk factors include a higher body mass index (BMI) and structural foot deformities [3–5, 7], such as hammertoes and hallux valgus [12, 13].

Diabetic peripheral neuropathy (DPN) is a risk factor for the development of ulceration [14]. Over 30% of persons with diabetes will develop DPN [15], the incidence increasing with age [16, 17]. DPN can affect the autonomic, sensory and motor nervous systems. Sensory neuropathy interrupts the protective feedback mechanism of touch and pain [18]. Motor neuropathy results in compromised muscle innervation, reduction in strength and, combined with limited joint mobility, the development of foot deformities. These deformities may lead to an increase in plantar foot pressures, particularly in the forefoot [19–22]. Autonomic neuropathy leads to diminished sweating and changes to skin perfusion, leading to dry skin and hyperkeratosis. As skin integrity is compromised, patients are more susceptible to trauma which may predispose a diabetic foot ulcer [22–25].

Neuropathic foot ulcers in persons with diabetes occur mostly at the plantar forefoot [12, 26, 27] and correspond to areas of peak plantar pressure (PPP) [28]. Bennetts et al. [29] demonstrated that most peak pressure areas are located in the forefoot regions in this population. A limited range of motion at the forefoot joints is also likely to contribute to the increased PPP observed in this region [30]. For this reason, plantar pressure mapping is used to guide footwear and insole manufacture and judge their effectiveness [31].

Reducing plantar pressures is considered a key factor for wound healing and the prevention of ulcer recurrence [32, 33]. Footwear and insoles are important treatment modalities for offloading these pressures [34, 35]. The desired offloading threshold should be <200 kPa to ensure ulcer-free survival at the forefoot [36]. Some studies also recommended that a pressure relief of 25–30% compared with the baseline be effective [31, 37]. The evidence for effective design characteristics of footwear and insole that can reduce plantar pressure is limited in the literature [38], and further exploration of the various design and modifications of footwear and insole can bridge the gap in the literature [39, 40].

### The rationale for performing the study

There is no existing, evidence-based recommendation for overall footwear and insole design that includes all technical specifications to offload the diabetes-related and neuropathic foot [38–40]. Several studies have suggested components of footwear design, such as the rocker sole profile, as the preferred design feature to offload PPP at the forefoot [31, 41–45]. Arts et al. [46] in the Netherlands and Rizzo et al. [43] in Italy conducted studies to test the effect of footwear design suggested by the consensus-based algorithm proposed by Dahmen et al. [47]. Both studies found that the footwear and insole design is effective in offloading the neuropathic diabetic foot. However, Arts and colleagues [46] found that the algorithm is not as effective for footwear specifications when offloading plantar pressure at the metatarsal heads is required.

Several studies [31, 43, 45, 48–50] have explored patient satisfaction and adherence to wearing footwear and insoles. Patient adherence to wearing therapeutic footwear is important to ensure improved offloading and ulcer prevention [43, 45, 48].

### Research aim

The aim of this study is to identify clinically relevant footwear and insole design and modification parameters that effectively offload forefoot PPP in the neuropathic feet of people with diabetes and increase adherence.

### Objectives

The research questions are:What factors and parameters need to be considered when prescribing footwear and insoles for people at risk of neuropathic forefoot plantar ulcer occurrence and recurrence?How can participants’ preferences be incorporated into footwear and insole design to increase the adherence to prescribed footwear in people with diabetes and neuropathy who are at risk of plantar forefoot ulcer occurrence and recurrence?

### Expected outcomes

The overall goal of this intervention is the prevention of ulceration; however, ulceration is an undesirable outcome for participants, so a proxy measure, which is a reduction of plantar pressure using footwear, is used as the primary outcome measure instead.

The expected outcome of the study is an algorithm or best practice recommendations that can be personalised to prescribe footwear and insole design and modifications based on individual pathologies, comorbidities and lifestyles in people with diabetes and peripheral neuropathy who are at risk of plantar forefoot ulceration. This algorithm or best practice recommendation is expected to provide a clear guideline for referrers, patients, prescribers and technicians to design or modify footwear and insole to ensure adequate and effective offloading of the forefoot to prevent the occurrence and recurrence of plantar neuropathic ulcers in people with diabetes.

The recommendations are expected to influence better optimise health service models and health fund’s resource allocation to maximise the impacts.

## Methods

### Trial design

The trial design is shown in the flowchart (Fig. 1).

**Fig. 1 Fig1:**
[figure not shown]
Trial design flow for the N-of-1 trial

### Methodological approach

The study will be comprised of a single patient or N-of-1 trial.

N-of-1 trials are usually randomised, often double-blind, and involve multiple crossover comparisons of an intervention and a control treatment [51, 52]. Oxford Centre for Evidence-Based Medicine has recommended this trial as level 1 evidence for treatment decisions [53].

N-of-1 trials provide a technique to guide evidence-based treatment decisions for an individual patient. They use common methodological components of large clinical trials to measure treatment effectiveness in a single patient. They are a practical alternative when circumstances do not allow for large-scale trials, such as rare diseases or comorbid conditions, or when participants use concurrent therapies [54]. However, the findings from these trials can be used to inform the development of algorithms to guide complex treatments for other patients. In this case, the complexity of the intervention (footwear and insole design) and the individually tailored nature of the intervention lend itself to an N-of-1 trial. This is also a more cost-effective approach than traditional phase three clinical trials [55].

Methodologically robust N-of-1 trials objectively assess the effectiveness of treatments within individual participants. Aggregation of multiple cycles identically conducted N-of-1 trials yields a population estimate of effect, which approximates the similar effect derived from other RCT designs. Trial participants contribute data for both intervention and control treatments creating matched data sets while using generally smaller sample sizes than conventional RCTs [51].

Single-patient or N-of-1 trials are commonly used for personalising the treatment options when participants have a chronic condition [56]. Recent studies suggest that N-of-1 trials are effective tools for improving therapeutic precision, and they are widely accepted by patients and clinicians as an effective modality because they are patient-centred [56, 57]. They also have proven value in guiding a more effective prescription [55, 57, 58]. In the era of ‘personalised medicine’, they are becoming more popular. It is increasingly clear that ‘one size does not fit all’, particularly in complex interventions like diabetic footwear design and modifications.

In this proposed study, participants will have an initial assessment with the principal investigator, having been referred from the high-risk foot service. The initial assessment will include the selection of appropriate footwear, measuring, casting and 3D scanning of feet and technical specification of footwear and insole that reflects participant’s preferences. Barefoot static and dynamic pressure and in-shoe pressure measurements will be carried out. Current (standard) footwear, which may be a regular retail shoe, orthopaedic footwear, post-op shoes or cam-walkers or moon boots with or without insoles (custom or prefab), will be used as the control arm for the trial.

The second assessment will be done once the footwear and insole are ready for fitting (generally within 4 weeks after the initial assessment and measurement). In-shoe pressure analysis will be carried out in the new footwear and insole, which may undergo minor or major modification to achieve desired offloading efficacy. Participants will be assessed for walking comfort and satisfaction with their new footwear. Scores will be recorded on a Likert scale [59]. A third consultation will be arranged 2 weeks later. New footwear-wearing instructions will be provided to the participants, including contact details for an emergency or experiencing any adverse effect from the new footwear.

In the third assessment, the participant’s feet will be assessed for any redness or rubbing and any discomfort from the footwear. The participant’s self-reported wearing period data will be collected and analysed for wear patterns and frequency. The footwear will be assessed for any unusual wear marks or pressure points. Necessary adjustments will be made, and the fourth review session will be booked for a monthly visit.

During the fourth assessment, the participant’s feet and footwear will be assessed again. Participants’ satisfaction with the footwear will be recorded and compared with the participant’s self-reported wearing period data for the previous month. A similar process will follow, and another monthly appointment will be made with the researcher.

In the fifth assessment, a similar process will follow as the previous review, and this is the endpoint of the study. Participants will be asked about the walking comfort and likeliness of footwear and suitability for the intended application. Overall feedback and any comments from the participants on the footwear will be recorded. Any repair or adjustments to the footwear and insoles will be carried out, and they will be given contact details for any future repair and follow-up reviews.

Double-blinding is not feasible in this study design, given the nature of the intervention and secondary outcomes. Blinding is recommended in N-of-1 trials, but it is not mandatory [52]. In this proposed study design, participants will need to be aware of the prescribed footwear in order to provide feedback on acceptance. Features of the footwear and insoles may be easily identifiable by clinicians in the team. However, the statistician will remain blinded, and this study design can be termed a single-blind trial [60, 61].

### Reporting standard

The quality of any study is dependent on the reporting standard of the study. To increase validity and acceptability, this N-of-1 trial will report data as per CONSORT extension for reporting N-of-1 trials (CENT) 2015 Statement [54].

### The rationale for the N-of-1 trial

Patient adherence is key for successful offloading initiatives of the neuropathic diabetic foot. Footwear is an integral part of clothing. Patient preferences play a vital role in footwear usage and adherence to recommendations. Therefore, a patient-centred study design that can recommend a precise prescription on personalised therapy/devices is important. The N-of-1 trial design is unique in that it allows a focused assessment of patient preferences and circumstances. This is also beneficial for personalised treatment decisions for patients with chronic conditions [56]. There is a direct clinical application in individualising each participant’s treatment with outcomes generalisable to a broader patient population [56].

The effectiveness of offloading will be measured using the in-shoe plantar pressure analysis system. Using in-shoe plantar pressure measurements and [62] analysis is the gold standard in footwear-based pressure reduction studies [31, 63].

This trial methodology is preferable to participants as they feel more involved in treatment decisions and see changes being made in response to their feedback [51].

### Rationale for control

The primary outcome measure is the reduction of forefoot peak plantar pressure. The control will be participants’ existing, usual footwear and insoles in the form of regular, orthopaedic or post-op footwear. This will form the baseline data of in-shoe plantar pressure measurements to be compared against the new footwear and insole to evaluate offloading efficacy. Hence, the choice of a control arm is essential, but in this case, the patient is their own control.

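### The study is justified as an N-of-1 trial, but the conduct described is a single fixed-order before-after comparison, so the level 1 and RCT-approximation claims do not carry over to it

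*Protocol article*

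**What the plan says.** The design is named under Methodological approach: "The study will be comprised of a single patient or N-of-1 trial". The same section describes what such trials are: "N-of-1 trials are usually randomised, often double-blind, and involve multiple crossover comparisons of an intervention and a control treatment". It then cites an evidence-grading body that "has recommended this trial as level 1 evidence for treatment decisions", and adds: "Aggregation of multiple cycles identically conducted N-of-1 trials yields a population estimate of effect, which approximates the similar effect derived from other RCT designs". The rationale for the N-of-1 trial goes further and presents the outcomes as generalisable to a broader patient population.

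The conduct is set out elsewhere in the same article.

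- **Abstract, Methods:** "This trial is non-randomised and unblinded".
- **Methodological approach and Rationale for control:** in-shoe pressure in the participant's current footwear is taken at the initial assessment. Of this reading the article says: "This will form the baseline data of in-shoe plantar pressure measurements to be compared against the new footwear and insole to evaluate offloading efficacy".
- **Methodological approach and Intervention description:** new footwear and insoles are fitted, generally within 4 weeks. They are then modified and remeasured until the pressure reduction is acceptable and the participant is satisfied.
- **Participant timeline:** t1 is the fitting, t2 comes 2 weeks later, and t3 and t4 follow at 4-week steps.
- **Outcomes:** success is PPP below 200 kPa or a 30% reduction from control. In-shoe pressure is measured at every fitting and review visit.
- **Data analysis:** one group-level paired t-test compares pressure in the study footwear with baseline or control footwear.

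**The concern.** The evidence claims attached to N-of-1 trials come from repeating the control-versus-intervention contrast within each person, preferably in random order. Repetition shows how much of a person's difference is noise. Alternation keeps change over time from being counted as treatment effect. The schedule described here has neither feature, yet the article uses the claims to justify the design.

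Two things are at stake. First, the individual result is the stated purpose of the design and is meant to feed a prescribing algorithm, but it would rest on a contrast that is never replicated. Second, any change between t0 and later visits in sensor calibration, body weight, foot volume or walking pace is counted as an effect of the footwear. Readers told that the design yields level 1 evidence would not expect either weakness. The Limitations section mentions only COVID-19 restrictions.

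**Working it through.** The plan gives no figure for this point: no within-person variability, and no power calculation behind the 21 participants. The check is therefore mainly structural, with illustrative arithmetic on stated assumptions.

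**Step 1: schedule.** From t0 to t1 is about 4 weeks, then 2, 4 and 4 weeks: 4 + 2 + 4 + 4 = 14 weeks. At 52/12 = 4.33 weeks per month this is 3.2 months, which agrees with the stated 3 to 4 months. New footwear is thus measured at about weeks 4, 6, 10 and 14, and control footwear at week 0.

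**Step 2: claimed properties against described conduct.**

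| Property invoked | Conduct described |
|---|---|
| Usually randomised | Non-randomised; always old footwear, then new |
| "involve multiple crossover comparisons of an intervention and a control treatment" | One switch; no return to control described |
| "Aggregation of multiple cycles identically conducted N-of-1 trials yields a population estimate of effect" | No repeated cycle; the footwear may be altered between readings, so t1–t4 are not replicates of one intervention |

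**Step 3: what depends on the control reading.** Write C for control pressure, N for new pressure at a later visit, and v for a visit-level shift on the log scale. Then

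log(N/C) = footwear effect + (v_later − v_0) + noise.

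With one order and no return to control, the average of (v_later − v_0) cannot be separated from the footwear effect. The 30% limb (N/C ≤ 0.70) and the paired t-test both contain C. The <200 kPa limb does not.

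**Step 4: precision of one participant's result.** Assume a within-person CV per reading of 5% to 10%, one control reading, and four new readings treated as exchangeable.

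SE of the log ratio = sqrt(CV² + CV²/4); interval for the ratio = 0.70 × exp(±1.96 × SE).

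- CV 5%: SE = sqrt(0.0025 + 0.000625) = 0.0559. The ratio is 0.627 to 0.781, a reduction of about 22% to 37%.
- CV 10%: SE = sqrt(0.01 + 0.0025) = 0.1118. The ratio is 0.562 to 0.871, a reduction of about 13% to 44%.

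These intervals contain noise only. A visit-level change of 10% in the ratio would come on top: 0.70 × 1.10 = 0.77 and 0.70 × 0.90 = 0.63, so a true 30% reduction would read as 23% or 37%.

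**Step 5: the group test.** Take n = 21, a two-sided 5% level and no footwear effect. Suppose pressure is lower at later visits by a common shift. The noncentrality is −ln(1 − shift)/SD × sqrt(21), where SD is the assumed standard deviation of the log ratio. For SD 0.10, 0.20 and 0.30:

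- 5% shift: rejection in 61%, 20% and 12% of trials.
- 10% shift: rejection in 99.6%, 63% and 34% of trials.

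The calculation is on the log scale, and the shifts and SDs are assumptions. It shows sensitivity to drift, not that drift occurs.

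**The case against.** The strongest reply is that the N-of-1 statements are general background, hedged by words such as usually, and that the article openly says the trial is not randomised. That is true, but it does not settle the matter. The section introduces these properties to justify this study and never says that they do not apply to it. The only departure it defends is the lack of double-blinding.

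Other objections narrow the point, and they stand.

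- A reader might infer that control footwear is measured only once. No sentence says so. The Outcomes section does not name the footwear worn at reviews, and Fig. 1 is not shown. What can be said is that no later control measurement is described and that control is treated as baseline.
- A reader might infer that visit differences fall on the contrast unchecked. The Outcomes section specifies a walk calibration, recorded body weight and a pace that is consistent at each measurement. These steps reduce visit-to-visit change but do not remove confounding with time and order.
- A reader might infer that the whole primary outcome fails. The <200 kPa limb needs no control value.
- A reader might take a narrower interval from paired sessions as proof that pairing is needed. At a CV of 10%, four pairs give SE = sqrt(0.02/4) = 0.0707. Four control readings at t0 with four new readings give sqrt(0.01/4 + 0.01/4) = 0.0707 as well. The gain comes from the extra control readings. The case for same-session pairing is only that shared visit shifts cancel.

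**Conclusion.** The point holds as a mismatch between the label with its evidence claims and the conduct described. On the text available, this is a series of single-participant before-after comparisons in fixed order, analysed as one group. The level 1 and RCT-approximation properties depend on repeated cycles that are not described, so they do not transfer. The 30% limb and the paired comparison are confounded with time and order; the <200 kPa limb is not.

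This conclusion needs no numerical assumption. Its size for an individual does: an observed 30% reduction carries a 95% interval of about 22–37% at a CV of 5% and 13–44% at 10%. That treats readings on possibly modified footwear as exchangeable and is not an analysis the article plans. The documents do not support a claim that the pressure result is biased by any particular amount, or that repeat control walks are required for the study to be useful.

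**What to change.** **Main change, wording only.** In the Abstract (Methods and Discussion), Methodological approach and The rationale for the N-of-1 trial, describe the study as a series of single-participant (single-group) before-after comparisons. State that the level 1 and RCT-approximation properties of repeated-cycle N-of-1 trials do not apply to it. Add to Limitations that the pressure contrast is confounded with time and order for the 30% limb and the paired test. The cost is a less favourable evidence claim.

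**Optional, for remaining visits, if the treating team and the ethics committees agree.** Measure control and study footwear in the same session, in random order, and analyse the session-level log ratio. Report how many participants lack a repeat control reading, and why. Whether any participant should walk in the old footwear is for the treating team to decide. The cost is an amendment through the ethics committees and site governance offices, and an extra walk of up to 12 m per session. Control data would also be incomplete, and possibly selectively missing, for participants already enrolled or judged unsuitable. Recruitment had begun in May 2021 and was due to finish by April 2022, so this step may reach only part of the sample and does not replace the wording change.
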